## 2 Materials and methods

### 2.1 Study design

The purpose of this pre- and post-quasi-experimental study will be to compare the immediate effect of trunk stabilization exercises on recovery of impaired core and postural stability induced by fatigue with that of foam rolling exercises in male and female sedentary adults. The protocol will be implemented and documented according to the Standard Protocol Items: Recommendations for Interventional Trials Statement (SPIRIT). The study design is provided in Figure 1. The research has obtained approval from both the ethics committee at the Faculty of Physical Education and Sport, Comenius University in Bratislava (Approval No. 5/2022), as well as the Ethics Committee of Kerman University of Medical Sciences (Approval No. IR. KMU.REC.1401.386). The study was also registered in the Clinical Trials system under the reference IRCT20221126056606N1.

**FIGURE 1 F1:**
[figure not shown]
Flow diagram of the study protocol.

#### 2.1.1 Ethical considerations and informed consent

This study will be conducted by the ethical principles outlined in the Declaration of Helsinki. All participants will be provided with detailed information about the purpose, procedures, potential risks, and benefits of the study. They will be informed that their participation is voluntary, and they will have the right to withdraw from the study at any point without any consequences. Written informed consent will be obtained from each participant before their inclusion in the study.

#### 2.1.2 Data and safety monitoring plan (DSMP)

This study involves non-invasive interventions, so a formal Data Safety Monitoring Plan (DSMP) or Data Safety Monitoring Board (DSMB) will not be implemented. However, the research team will actively monitor participant safety throughout the study and address any adverse events promptly. All procedures are designed to minimize risk and ensure participants’ wellbeing.

### 2.2 Participants and setting

A total of 20 sedentary employees of universities ages 25–44 years, comprising 50% men and 50% women, will participate in this study. This study will be carried out at the Faculty of Physical Education and Sports, Comenius University in Bratislava, Slovakia.

### 2.3 Inclusion and exclusion criteria

Participants will be selected based on the following criteria: Sedentary adults aged 25–44 years who report sitting continuously for a minimum of 2 hours on any given working day (Saiklang et al., 2022a). The International Physical Activity Questionnaire [IPAQ] will be used to screen potential study participants to determine whether they are sedentary. Potential participants who meet any of the following criteria will be excluded: a history of femoral, spinal, or intra-abdominal surgery within the past 12 months (Sitthipornvorakul et al., 2015); pregnancy (Abboud et al., 2014); participants having been diagnosed with congenital arthritis, spine and disc infections, rheumatoid arthritis, spondylolisthesis, ankylosing spondylitis, spinal anomalies, spondylosis, tumors, systemic lupus erythematosus, or osteoporosis will be excluded (Sitthipornvorakul et al., 2015). Additionally, individuals who have received physiotherapy services within 1 month prior to the study’s commencement (Fortun-Rabadan et al., 2021) or have experienced any form of mental health disorder, including depression and anxiety, within the last 3 years (Fortun-Rabadan et al., 2021) will also be excluded. Furthermore, participants will undergo health screenings before the study to rule out infections or symptoms of fatigue (White, 1997). They will also disclose any musculoskeletal disorders experienced in the last 6 months, including acute or chronic low back pain. To ensure the validity of the inclusion and exclusion criteria regarding low back pain, we will administer the Oswestry Low Back Pain Disability Questionnaire (Fairbank JC 1980) for pain assessment. Additionally, a BMI <30 will be used to screen for overweight or obesity. To further ensure only metabolically healthy individuals are included, participants with major medical disorders or metabolic conditions such as diabetes, hypertension, hyperlipidemia, or related diseases will be excluded.

#### 2.3.1 International physical activity questionnaire

The International Physical Activity Questionnaire [IPAQ] will be used to identify those who are sedentary in order to screen potential study participants The IPAQ is a standardized self-report instrument specifically crafted to evaluate physical activity levels within an individual’s typical daily routine (Mehta et al., 2018). There are two versions of this questionnaire, long and short (Demircioğlu et al., 2021). The IPAQ Long Form (IPAQ-LF) is typically employed in clinical settings or research studies to gauge physical activity levels. In contrast, the IPAQ Short Form (IPAQ-SF) is utilized to screen physical activity levels within the general population (Mehta et al., 2018). The objective of both versions of the questionnaire is to evaluate the quantity and intensity of physical activity that an individual engages in on a weekly basis (Mehta et al., 2018). Each version of the questionnaire encompasses four domains of physical activity, which include work-related activities, leisure-time physical activity, domestic and gardening activities, and transport-related activities. Additionally, sedentary time, defined as time spent in a seated or reclined position during waking hours, is recorded for both a typical weekday and weekend day within the same time frame (Ruescas-Nicolau et al., 2021). In the present study, the long version IPAQ will be used, which contains 27 items across four domains (Mehta et al., 2018). With the long form, it is possible to compute scores specific to each domain, as well as scores tailored to individual activities, and continuous scores. Continuous scores are expressed in metabolic equivalent minutes (MET) as a metric for quantifying physical activity. People are categorized into low, moderate, or high levels of physical activity based on these scores (Mehta et al., 2018).

### 2.4 Sample size estimation

Sample size estimation was conducted utilizing the G*Power software package (version 3.1.9.7) based on the methodology outlined in the study by Fonta et al. (2021). The input parameters included the following: the statistical test was repeated measures, within factors; the α error probability was 0.05; the effect size F was 0.25; power (1 − β error probability) was 0.80; correlation among repeated measures was 0.70; and no sphericity correction (e = 1) was applied. It is important to note that the magnitude of the correlations (r = 0.7) can be considered large according to Hopkins et al. (2009). This correlation was chosen to reflect the anticipated relationship between the repeated measures in this study, based on the literature (Hopkins et al., 2009; Fonta et al., 2021; Zahiri et al., 2022). Consequently, the total sample size was determined to consist of seven subjects (in each trial). To ensure ample statistical power, especially in scenarios with smaller-than-expected effects or lower correlations between repeated measures, we decided to include 20 participants, who will be tested in the three experimental conditions. This approach also takes into account the possibility of participant dropouts during the study.

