#### 2.5.2 Experimentation

The experiment involves 20 participants, each completing three sessions spaced 1 week apart. In each session, they will perform a modified Abt’s fatigue protocol, consisting of eight exercises targeting their core muscles. Subsequently, they undergo recovery modalities. Everything will remain the same throughout the sessions except the type of recovery modality, which will be varied (trunk stabilization exercises, foam rolling exercises, and passive recovery). The order of the recovery modalities will be counterbalanced to control for potential sequence effects. Data will be gathered from participants at three different time points:1. Pre-fatigue assessment (baseline measurement).2. Post-fatigue assessment (immediately following the fatigue protocol).3. Post-recovery modalities assessment (immediately and 15 min after the completion of active and passive modalities, respectively).

Participants will be tested by the same examiners at the same time.

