### 2.7 Statistical analysis

The statistical analysis will employ SPSS Statistics software (Version 24; IBM Corporation^©^, United States). To evaluate the normality of core and postural stability, as well as EMG variables, a Shapiro-Wilk test will precede any comparative analyses. For normally distributed data, a two-way ANOVA will be applied to explore the main effects of recovery modalities and time intervals, along with any potential interactions between these factors. The factors under consideration include the type of conditions [trunk stabilization exercises session, foam rolling exercise session, passive recovery] and testing time [T1: baseline, T2: immediately after modified Abt’s fatigue protocol, T3: immediately after recovery modalities, and T4: 15 min after recovery modalities]. To identify significant differences, Bonferroni *post hoc* comparisons will be conducted as necessary.

For non-normally distributed data, nonparametric tests will be utilized. Friedman’s test, followed by Dunn’s *post hoc* test, will be employed to compare core and postural stability, as well as EMG variables across testing times [T1, T2, T3, and T4]. The Kruskal-Walli’s test will be utilized for between-condition mentioned above comparisons at each testing time.

Data will be presented as mean ± standard deviation (SD). Effect sizes for both between-session and within-session comparisons of all quantitative variables will be evaluated using Cohen’s d coefficient: small effect (d < 0.2 and ηp2 = 0.01); moderate effect (d ≈ 0.5 and ηp2 = 0.06); and large effect (d > 0.8 and ηp2 = 0.14) (Cohen, 2013). The significance level (α) will be established at 0.05 for all statistical tests.

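### Dropouts are expected, but the two-way ANOVA, run in its usual repeated-measures form, would drop any participant missing one of 12 values; a mixed model would keep the partial data

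*Protocol article*

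**What the plan says.** Section 2.4 (Sample size estimation) describes the calculation thus: "the statistical test was repeated measures, within factors". It arrives at seven and then raises the number: "we decided to include 20 participants, who will be tested in the three experimental conditions". Three reasons are given for the increase: smaller effects than expected, lower correlations than expected, and dropouts. On the last it says "This approach also takes into account the possibility of participant dropouts during the study". No dropout rate is stated.

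Section 2.5.2 (Experimentation) has the 20 participants "each completing three sessions spaced 1 week apart". Section 2.1.1 allows withdrawal at any point.

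Section 2.7 (Statistical analysis) names SPSS version 24. For normally distributed data, "a two-way ANOVA will be applied to explore the main effects of recovery modalities and time intervals", together with their interaction. The factors are three conditions and four times, T1 to T4. The words repeated measures are not used there. Non-normal data go to Friedman's test across times and to a Kruskal-Wallis test between conditions at each time. The article describes no method that would use the data of participants who complete only part of the schedule.

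**The concern.** The article states an expectation (people will drop out) and a method (two-way ANOVA over within-participant factors) that fit each other poorly. The usual SPSS repeated-measures procedure lays the 12 values out as 12 columns and uses only complete rows. A missed session leaves four columns empty and removes the participant from every such ANOVA, although the other sessions were measured. A single failed recording removes the participant from the ANOVA of that variable only. Extra head-count makes up for lost numbers, but the sessions that incomplete participants did finish are still unused.

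What is at stake is mainly precision, in a trial of 20 people. A secondary matter is that, if missing values are related to how well people perform, a complete-case analysis changes who is compared.

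**Working it through.** **The plan's own figure.** Inputs from section 2.4: f = 0.25, α = 0.05, power 0.80, r = 0.70, ε = 1. The number of measurements m is not stated. With one group, λ = f²·N·m/(1 − r), df1 = m − 1 and df2 = (N − 1)(m − 1):

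| Test | N for 80% power | Power at N = 7 |
|---|---|---|
| m = 3 | 17 | 0.36 |
| m = 4 | 15 | 0.42 |
| m = 12 | 8 | 0.75 |
| 3 × 4 interaction, df1 = 6, 12 cells in λ | 7 | 0.84 |

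Only calculations that count all 12 cells as repeated measurements come to about seven. This supports reading the planned ANOVA as a within-participant analysis of 3 × 4 = 12 values.

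**Missed sessions: what listwise deletion costs.** Take total variance 1 and use the protocol's r = 0.70 as the correlation between sessions (an assumption), so the within-participant variance is 0.3. Spread the losses evenly over modalities. The information about a modality contrast is then

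- 1/0.3 = 3.333 from a participant with three sessions,
- on average (2/3)(1/0.51) + (1/3)(0.70/0.51) = 1.765 from one with two sessions, where 0.51 = 1 − 0.70²,
- on average 1/3 from one with a single session.

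The contrast variance is 2 divided by the summed information. With all 20 complete it is 2/66.67 = 0.0300.

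| Assumed loss | Listwise deletion | All data used | Listwise larger by |
|---|---|---|---|
| 2 miss one session | 2/60.00 = 0.0333 | 2/63.53 = 0.0315 | 6% |
| 3 miss one session | 2/56.67 = 0.0353 | 2/61.96 = 0.0323 | 9% |
| 6 miss one session | 2/46.67 = 0.0429 | 2/57.25 = 0.0349 | 23% |
| 6 leave after one session | 2/46.67 = 0.0429 | 2/48.67 = 0.0411 | 4% |

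**Lost values: how many participants remain.** If a share p of values is lost independently, 1 − (1 − p)¹² of participants are incomplete for that outcome. If the same share is lost as whole sessions, the figure is 1 − (1 − p)³.

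| p | Scattered single values: lost (left of 20) | Whole sessions: lost (left of 20) |
|---|---|---|
| 1% | 11.4% (17.7) | 3.0% (19.4) |
| 2% | 21.5% (15.7) | 5.9% (18.8) |
| 3% | 30.6% (13.9) | 8.7% (18.3) |

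**Power with complete cases only.** For the three-level modality comparison (m = 3), power is 0.87, 0.83, 0.77 and 0.71 at N = 20, 18, 16 and 14. If all 12 cells count (m = 12), it is still 0.99 at N = 14.

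**The case against.** Several counter-arguments have force.

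- *Handling of missing data belongs in the analysis plan.* True in general, and a missing imputation rule would be no finding. Here, however, the article itself names both the expected dropouts and the method.
- *Section 2.7 does not say repeated measures.* This stands. A reader might infer that the article prescribes a complete-case analysis; it does not. An ANOVA on long-format data with participant as a random factor would keep partial records. The point depends on the usual SPSS form, which section 2.4 and the crossover design make the natural reading.
- *The nonparametric branch is different.* This stands. Friedman's test needs the four times within one condition, and Kruskal-Wallis uses whatever is present at each time. Neither needs 12 complete values.
- *The larger figures are favourable cases.* This stands. Six of 20 missing a session is 30%, and independent loss of single values is the pattern that hurts most. Dropouts lose whole sessions, and at 1% to 3% that removes only 3% to 9% of participants.
- *Twenty far exceeds seven.* A reader might infer that the trial becomes underpowered. The documents do not support that: even 13.9 complete participants is about twice the stated requirement. The margin is thin only if the relevant test has three or four levels (17 or 15 needed), and whether seven is right is a separate question.
- *Bias is speculative.* A reader might also infer that listwise deletion will bias the comparison. Nothing in the article shows that withdrawal depends on modality; the fatigue protocol is the same in every session and the order is counterbalanced. Nor would a mixed model remove bias from dropout that depends on unobserved response.

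**Conclusion.** The point holds as one of efficiency and of fit between stated expectation and stated method. Run in its usual repeated-measures form, the planned ANOVA discards completed sessions of participants whom the plan expects to lose in part. The cost depends on losses that the documents do not quantify. It is modest for a few missed sessions (6% to 9% more variance for 2 or 3 participants), larger for six (23%), and small if leavers contribute only one session (4%). It is greatest if single recordings are lost here and there, when 1% to 3% of values would remove 11% to 31% of participants from that outcome. These figures assume even losses over modalities and a between-session correlation of 0.70 for the variances, and independent losses for the percentages. The planned analysis is not shown to be biased or the trial underpowered. The change is worth making because it costs little.

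**What to change.** In section 2.7, replace the two-way ANOVA by a linear mixed model in the same software, fitted to all available observations. Include fixed effects for modality, time and modality × time, and random effects for participant and for session within participant. A fixed effect for session number is optional. Report the modality contrasts at T3 and T4 from this model. This also makes the within-participant structure explicit.

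The cost is a change of analysis wording and slightly more work at analysis, with no new participants, visits or measurements. The model relies on data being missing at random, which should be said. With complete data and a matching covariance structure, its results would be essentially those of the repeated-measures ANOVA, so little is lost if nobody drops out.

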### 2.5 Procedures

The study will follow a structured protocol consisting of two main phases: familiarization and experimentation. During the familiarization phase, participants will be introduced to the fatigue protocol, recovery modalities, and assessment tools. In the experimentation phase, the modified Abt’s fatigue protocol will be implemented, where participants perform core exercises aimed at inducing fatigue in the trunk muscles. This will be followed by different recovery modalities. The evaluation will include pre-fatigue, post-fatigue, and post-recovery assessments, focusing on muscle fatigue, postural and core stability, and the flexibility of the back and hamstring muscles.

#### 2.5.1 Familiarization

In the first phase, a familiarization session will be performed about 1–2 h before data collection. Participants will be informed about the study’s objectives and procedures prior to participating in the research. During the second phase, participants will be tasked with completing a questionnaire detailing their baseline and personal characteristics. Height will be assessed using a single stadiometer, while body mass will be measured with a calibrated digital scale. The weights utilized in the fatigue protocol will be determined individually for each participant through the familiarization process. This involves finding the heaviest weight that participants can perform correctly 20 times in 40 s (Askari and Esmaeili, 2021). Throughout this period, participants will be instructed to maintain their regular diet and avoid engaging in strenuous exercise or consuming performance-enhancing energy drinks, medications (such as antidepressants or pain medications), drugs, or caffeine for 48 h leading up to the data collection sessions (Williams et al., 1987; Tarnopolsky, 2008; Armstrong et al., 2018; Bergefurt, 2023).

#### 2.5.2 Experimentation

The experiment involves 20 participants, each completing three sessions spaced 1 week apart. In each session, they will perform a modified Abt’s fatigue protocol, consisting of eight exercises targeting their core muscles. Subsequently, they undergo recovery modalities. Everything will remain the same throughout the sessions except the type of recovery modality, which will be varied (trunk stabilization exercises, foam rolling exercises, and passive recovery). The order of the recovery modalities will be counterbalanced to control for potential sequence effects. Data will be gathered from participants at three different time points:1. Pre-fatigue assessment (baseline measurement).2. Post-fatigue assessment (immediately following the fatigue protocol).3. Post-recovery modalities assessment (immediately and 15 min after the completion of active and passive modalities, respectively).

Participants will be tested by the same examiners at the same time.

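### Order is counterbalanced over three weekly sessions, but the ANOVA has no session term, so any session shift stays in the error of the modality comparison

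*Protocol article*

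**What the plan says.** Section 2.5.2 of the protocol article sets a within-person design: "The experiment involves 20 participants, each completing three sessions spaced 1 week apart". Only the recovery modality changes between sessions, "which will be varied (trunk stabilization exercises, foam rolling exercises, and passive recovery"). On order it says: "The order of the recovery modalities will be counterbalanced to control for potential sequence effects". It gives neither the number of orders nor how participants are assigned to them.

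Section 2.2 fixes the sample: "A total of 20 sedentary employees of universities ages 25–44 years, comprising 50% men and 50% women". Section 2.4 arrives at 20 as a margin over a computed seven and as an allowance for dropout. The number of orders plays no part.

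Section 2.7 states the model: "a two-way ANOVA will be applied to explore the main effects of recovery modalities and time intervals", with their interaction. "The factors under consideration include the type of conditions" (three levels) and testing time T1 to T4, all four within one session. Neither session number nor order is a factor. The fallback for non-normal data (Friedman across testing times, Kruskal-Wallis between conditions) has no session factor either.

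**The concern.** The plan expects order to matter, since that is its stated reason for counterbalancing. Its own procedures make a session effect plausible. Each participant is measured on the balance tasks at four testing times in each of three sessions, 12 rounds in all. The weights for the fatigue bout are set once, beforehand, while the bout is repeated weekly.

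Counterbalancing spreads such a shift over the modalities. It does not remove the shift from the data. With no session term, the shift ends up in the participant-by-modality variation against which the modality main effect is tested, and the test loses power. That matters more than usual here, because the abstract hypothesises that the two exercises are equally effective. An inflated error term favours a non-significant difference, which could be misread as support for that hypothesis. The sample size adds a smaller issue: 20 does not divide evenly over the orders.

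**Working it through.** **Inputs.** From Section 2.4: alpha 0.05, f = 0.25, correlation r = 0.70, no sphericity correction. From Sections 2.2 and 2.5.2: N = 20, three modalities, three sessions. Assumed, because the documents give no drift: outcome SD 1 and a linear shift D from session 1 to session 3 of 0, 0.5, 0.8 or 1.0 SD.

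**The plan's own figure.** With noncentrality f²·N·m/(1 − r) and error df (N − k)(m − 1), for k groups and m measurements, one group needs N = 17 for m = 3, 15 for m = 4 and 8 for m = 12. A group-by-time interaction with 3 groups and 4 times needs 19, which rounds up to 21 for equal groups, or seven per group. The stated seven is therefore reached only under settings that Section 2.4 does not give. The point here does not depend on this.

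**Balance.**
- Three modalities have 6 orders, or 3 in one Latin square. 20 = 3×6 + 2 = 6×3 + 2, so two participants are left over either way.
- There are 15 ways to add two different orders to three full sets of six. The bias is the difference between two modalities in their average session effect, for a shift that moves in one direction only.

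| Two surplus orders | Number of pairs | Counts per session | Bias, linear shift | Largest bias |
|---|---|---|---|---|
| No modality in the same session (ABC, BCA) | 6 | 7/7/6 in all sessions | 5% of D | 5% of D |
| Mirrored (ABC, CBA) | 3 | 8/6/6 in session 2, 7/7/6 in sessions 1 and 3 | 0 | 5% of D |
| Same modality first, or same modality last | 6 | 8/6/6 in session 1 or 3 | 7.5% of D | 10% of D |

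- Dropout widens this. With random loss of 2, 4 or 6 people, the 95th percentile of the largest gap between modalities in mean session position is 0.22, 0.38 or 0.50 sessions. A linear shift moves D/2 per session, so this is about 11%, 19% or 25% of D.

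**Error variance of the modality main effect.**
- Without a shift, the error variance is 1 − 0.7 = 0.3 on (20 − 1)(3 − 1) = 38 df.
- A linear shift (0, D/2, D) has squared deviations from its mean summing to D²/2 per person, so 20·D²/2 = 10·D² over 20 people.
- Inflation = 10·D²/(38 × 0.3) = 10·D²/11.4.
- D = 0.5: 2.5/11.4 = 22%. D = 0.8: 6.4/11.4 = 56%. D = 1.0: 10/11.4 = 88%.

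**Power and type I error.** With no shift, noncentrality is 0.0625 × 20 × 3/0.3 = 12.5. Power is 0.870 on 38 error df, and 0.868 on 36 df once session is in the model. Simulation with the mirrored pair, where a linear shift causes no bias, gives:

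| D (SD) | Power, no session term | Power, session term | Type I error, no session term |
|---|---|---|---|
| 0 | 0.87 | 0.87 | 0.05 |
| 0.5 | 0.80 | 0.87 | 0.03 |
| 0.8 | 0.69 | 0.87 | 0.01 |
| 1.0 | 0.58 | 0.87 | about 0.005 |

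With the term, type I error stays at 0.05. Other placements of the two extra orders give 0.82 to 0.86 at 0.5 SD and 0.63 to 0.73 at 1 SD without the term; these depend on which modality the residual bias happens to favour. With four dropouts, power is 0.68 without and 0.76 with the term at 0.5 SD, and 0.46 against 0.76 at 1 SD.

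**Interaction.** A shift that adds the same amount at T1, T2, T3 and T4 of a session drops out of every within-session change, and so out of condition-by-time. Only a change across sessions in the response to fatigue or recovery enters the error of the interaction.

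**The case against.** Four arguments carry weight.

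- **The text does not promise exact equality.** A reader might infer from the divisibility that 20 people cannot be counterbalanced. Counts within one of each other are ordinary counterbalancing, and they are achievable. This stands.
- **The bias is small.** A reader might infer that learning or adaptation distorts the modality comparison and produces false positives. Before dropout it does not: bias is 0 to 10% of the shift, and the type I error falls. This stands; the harm is mainly loss of power.
- **The plan already limits drift, and each session has its own baseline.** There is a familiarization phase (Section 2.5.1), and the fatigue bout is extended by perceived exertion (Section 2.5.4). Recovery is most naturally judged by the interaction, from which a constant session shift cancels. At 0.5 SD, power is still about 0.80. This limits the concern, but Section 2.7 also plans the modality main effect, and neither measure rules out learning over 12 rounds of tests.
- **Model detail belongs in an analysis plan that is not shown.** This does not stand. Section 2.7 names the model and both its factors, and session is not among them.

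A reader might also infer non-random assignment to orders from Section 2.1, "The purpose of this pre- and post-quasi-experimental study". That is a design label. Section 2.5.2 does not say how orders are assigned, and every participant receives all three modalities, so the documents do not support a selection claim.

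**Conclusion.** The analysis omits a factor that the design treats as important, and including it costs almost nothing. How much is lost depends wholly on the session shift, which the documents do not give. With no shift nothing is lost. At an assumed 0.5 SD the loss is about 7 points of power, and at 1 SD about 29 points. These figures are for the modality main effect on one outcome, with r = 0.7, f = 0.25, N = 20 complete and a linear shift. Imbalance of orders is secondary unless dropout is appreciable. This is an improvement that should be made, not an error that invalidates the trial.

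**What to change.** 1. **Model.** Add session (1 to 3) as a fixed effect to the condition-by-time model, with participant as a random effect. Include a participant-by-session random term so that the modality main effect keeps its own error. Error df for that effect go from 38 to 36. A session main effect does not absorb a change in fatigue or recovery response across sessions. If that is a worry, add session-by-time, a further (3 − 1)(4 − 1) = 6 df.
2. **Orders.** Keep n = 20. Assign participants from one pre-generated random list of three full sets of the six orders plus two surplus orders. To keep 7/7/6 in every session, choose two surplus orders that never put the same modality in the same session. A mirrored pair is an alternative: it gives 8/6/6 in session 2 but no bias under a linear shift. Avoid two orders that share their first or last modality.
3. **Sex.** Do not run separate blocks of six within each sex. Ten per sex is one full block and four of the next. Of the 15 × 15 = 225 combinations of partial blocks, 117 (52%) leave some modality with 5 or fewer participants in a session.
4. **Wording.** Describe the order as near-balanced with session adjustment, and state how participants are assigned to orders.

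The cost is 2 df for the session term and a prepared list, with no extra participants, visits or measurements.
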